### Randomization and allocation concealment

3.5

The researcher, who is not involved in the recruitment stage using R software to pre-generate a randomization list, which determined participant’s allocation to each intervention groups: arm 1(no frame message), arm 2 (gain-framed message) or arm 3 (loss-framed message). Subsequently, sealed envelopes containing group assignments were prepared by an independent researcher. Upon participant enrollment and completion of baseline assessments, an authorized team member opened the sealed envelope corresponding to each participant’s unique identification code to determine their group assignment. Furthermore, participants will not be informed of their group allocation until they provide written consent.

### The intervention procedure

3.6

The cardiovascular risk communication information will be delivered as standard health message about individual’s CVD risk and risk coping which not contain any particular message framing (arm 1), gain-framed message (arm 2) and loss-framed message (arm 3). Participants will be given the opportunity to withdraw at any point during the procedure.

#### Arm1: CVD risk communication based on no-framed message (control)

3.6.1

The CVD risk communication content will be derived from the Chinese CVD primary prevention guidelines (2023), CVD risk assessment and management guidelines (2019), Chinese guideline on healthy lifestyle to prevent CVD (2020), comprehensive prevention and treatment guidelines of CVD for community population (2020), Chinese guideline for lipid management (2023), et al., which includes two core message elements: “*why CVD risk is important?*” and “*why CVD risk is relevant to you?*.” To be more specific, the first message element includes the definition and etiology of CVD, the importance of CVD risk management; and the second message element includes *Your* CVD risk factors, risk value, risk effect and risk coping. The message elements and contents have been reviewed by 16 experts from the field of Cardiology (*n* = 3), general medicine (*n* = 3), CVD nursing (*n* = 4), community nursing (*n* = 3), public health (*n* = 1), health education and health promotion (*n* = 1), information communication (*n* = 1). Details of the intervention procedure can be found in Supplementary Table S2.

A total of 48 videos will be designed according to those risk communication contents, with 16 videos allocated to each intervention arm. Each video has a duration of 60 to 90 s to achieve optimal communication efficacy (52). The intervention will span a duration of 8 weeks, with participants receiving two sessions per week. These video sessions will be sent on Sunday and Wednesday morning between 7:00 and 9:00 a.m. weekly. This schedule will be tailored to the participants’ reading habits and working regulations to ensure the content does not adversely affect their work and sleep. Those videos will be transmitted to each participant through the mobile communication software WeChat. Subsequent to each video, participants will be prompted to respond two specific questions pertaining to the most notable keywords, as well as a central question regarding the content of the video. Their responses will ascertain that they have viewed the video carefully and comprehended its content thoroughly. In order to promote participant compliance, previous research suggests the utilization of financial incentives (47). As per the study protocol, participants who successfully answer both questions will be granted a reward of 1 RMB. After intervention procedure finished, all participants will receive a report of the CVD risk assessment and communication to further read and think aloud if necessary. Two weeks prior to the scheduled follow-up, participants will be sent a message containing details regarding the study procedure, as well as a reminder for the forthcoming 3-month follow-up.

#### Arm 2: CVD risk communication based on gain-framed message

3.6.2

Positive framing differed only in message presentation (40), the content of information was equivalent with the control group. The message will adopt a gain-framed approach, emphasizing the potential positive outcomes associated with a correct understanding of CVD risk and adherence to appropriate risk management behaviors. For instance, in the module titled ‘Your CVD risk value’, the statement provided to the gain-framed group will state that their risk of developing CVD within the next 10 years is 6.3%. This value exceeds the recommended ideal risk level of 4.4% (with the ideal level of modifiable risk factors). Consequently, out of a group of 100 men with the same age and laboratory results, it is projected that 6 individuals will develop CVD within the next decade. Additionally, two individuals will be exempt from CVD due to effective control of ideal risk factors. This information will be accompanied by two highlighted pictograms illustrating the potential benefits. In the module of ‘weight control’, the gain-framed group will be presented with the following statement: “Maintaining a healthy weight and waist circumference can be advantageous in controlling blood pressure, glucose, and lipid levels, thereby reducing the risk of CVD. Specifically, a reduction of 1 cm in waist circumference can lead to 1.48 times decrease in the 10-year CVD risk.” This statement will be accompanied by an illustrative image depicting individuals with healthy weight and waist circumference. The frequency and timing of video delivery will align with that of the control group.

#### Arm 3: CVD risk communication based on loss-framed message

3.6.3

Negative framing differed only in message presentation (40), and the information will focus on the adverse consequences that arise from a lack of proper understanding of CVD risk and the neglect of preventive behaviors.

For instance, in the module titled “Your CVD risk value,” the statement provided to the loss-framed group will state that their risk of developing CVD within the next 10 years is 6.3%, which exceeds the desired risk level of 4.4%. This indicates that out of a sample of 100 men with the same age and laboratory results, approximately 6 individuals will experience CVD within the next decade. Furthermore, an additional two individuals are expected to develop CVD within the same timeframe due to inadequate control of risk factors. This information will be accompanied by two highlighted pictograms illustrating the potential losses. In the module focused on weight control, the loss-framed group will be presented with the following statement: “Individuals who are overweight and have a higher waist circumference may experience greater difficulty in managing blood pressure, glucose levels, and lipid levels, consequently increasing their risk of cardiovascular disease. Specifically, a 1 cm increase in waist circumference is associated with a 1.48 times higher 10-year cardiovascular disease risk.” This information will be accompanied by a visual representation of obesity, particularly central abdominal obesity. The frequency and timing of video delivery will align with those in the control group.

### Outcomes and measurements

3.7

Two well-trained independent investigators, who are unaware of the group allocation, will conduct the outcome assessment in the chronic disease management clinic of each community. Baseline assessments will include demographic factors such as age, gender, marital status, education level, ethnic group, employment status, monthly income, subjective numerical ability (53) and medical history (hypertension/diabetes/dyslipidemia).

#### Primary outcomes

3.7.1

The primary outcome aims to assess two key aspects: (1) CVD prevention behaviors, encompassing healthy physical activity, a balanced diet, and adherence to preventative medication; and (2) CVD absolute risk.

Healthy physical activity will be assessed using the questionnaire of self-reported International Physical Activity Questionnaire-short version (IPAQ) (54). The responses were processed and aggregated using the IPAQ guidelines for Chinese (55). Participants who achieved a minimum of 150 min of moderate-intensity physical activities or 75 min of vigorous-intensity physical activities per week were considered to have fulfilled the criteria for adequate physical activity (56).

Healthy diet will be assessed through healthy diet score based on the updated Chinese Dietary Guideline (57). The assessment included the weekly consumption of six food groups, namely fresh fruit, fresh vegetables, whole grains, fish and other seafood (consumed more than once per week), bean and bean food (consumed at least four times per week), and red meat (consumed less than seven times per week). The response that met the established criteria received a score of 1 for each food group, and the cumulative score was calculated (with a maximum score of 6). The healthy group was defined as individuals with a total score of 4 or higher (58).

Taking preventative medication will be evaluated through medical prescription for stain/lipid lowering, anticoagulants, antihypertension, glucose-lowering medications (59), based on data obtained from the community physician health check system.

The estimation of CVD absolute risk, including both 10-year and lifetime CVD risk, will be performed using the China-PAR equation (50). Participants will be classified into three groups based on the China-PAR cut-off value specified in the Chinese guidelines (56), namely low risk (<5%), moderate risk (5–9.9%) and high risk (≥10%); for lifetime CVD risk: low risk (<32.8%), and high risk (≥32.8%).

#### Secondary outcomes

3.7.2

Secondary outcomes include CVD risk perception, efficacy belief, CVD related knowledge, major adverse cardiovascular events (MACE), the emotional response, physical indicators (Blood pressure, blood glucose, waist circumference and BMI) and other lifestyle related risk factors [smoking, drinking status, and subjective health status (60)].

CVD risk perception, efficacy belief and CVD related knowledge will be evaluated using the Chinese version of Attitude and Beliefs about Cardiovascular Disease Risk Questionnaire (ABCD-C) (49), which comprises 26 items across four dimensions. Efficacy belief will be assessed using the item 19, 20, 22, and 24, following the recommendation by Rimal and Juon (61). This scale has demonstrated good validity and reliability in both its original and Chinese versions, as evidenced by Cronbach’s α values ranging from 0.70 to 0.94. The emotional response will be assessed using two items on a 10-point scale (1–10; with a total range of 2–20), which have been adopted from the existing literature (62). An example of such item is “How concerned are you by reading this information?.” MACEs are defined as the composite endpoints of cardiovascular death, spontaneous myocardial infraction, and target vessel revascularization at 3 months follow up (63). The smoking and drinking status, as well as physical indicators, were extracted from the follow-up records of participants by GPs.

#### Other measurements

3.7.3

To assess the manipulation check, participants were asked to rate the extent to which they believed the video messages emphasized the advantages of engaging in CVD risk management or the disadvantages of not doing so. This rating was measured on a scale of 1 to 7, with 1 indicating a greater emphasis on the benefits, 4 indicating an equal focus on both benefits and risks, and 7 indicating a greater emphasis on the disadvantages (34). Participants will be deemed to have passed the manipulation check if they choose the item that aligns with their assigned message condition (64). The level of engagement will be evaluated based on the responses to questions following each video message, with a threshold of more than 75% of responses indicating high engagement (35). The qualitative components of risk communication experience after intervention procedure finished at 8 weeks will be evaluated using semi-structured interviews with the participants. This approach enables us to investigate participants’ experiences and delve into the social, cultural, and environmental factors that may impact their responses to the intervention. Such exploration is invaluable for interpreting quantitative findings accurately and enhancing intervention program effectiveness through iterative improvements. Details of the interview outline can be found in Supplementary Table S2. Study participants will be randomly selected at each study site among enrolled samples. The interviews will be stopped once data saturation is reached (Table 1).

**Table 1 tab1:** Research activities.

	Baseline	Post assessment	Follow-up assessment
	T0	T1	T2
Informed consent	√		
Demographic, socioeconomic assessment	√		
CVD risk factors assessment	√	√	√
10-year CVD risk calculation	√		√
Lifetime CVD risk calculation	√		√
Physical activity assessment (self-reported)	√	√	√
Healthy diet assessment (self-reported)	√	√	√
Medication prescription	√	√	√
CVD related knowledge	√	√	√
CVD risk perception	√	√	√
Health related efficacy	√	√	√
Subjective health status	√	√	√
Major adverse cardiovascular events (MACE)			√
Emotional response		√	
Manipulation check		√	
Participants engagement		√	
Interviews with participants		√	

### Statistical analysis

3.8

#### Data analysis

3.8.1

Descriptive statistical analysis will be conducted for all measurements. The distributions of categorical baseline variables will be compared using χ^2^ test among the three intervention groups. The difference in continuous variables will be analyzed using either one-way analysis of variance (ANOVA) or a non-parametric rank-sum test. The differential changes in the primary (i.e., healthy behaviors) and secondary (i.e., risk perception) outcomes at T1 and T2, relative to T0, across the three groups will be assessed using generalized estimating equations (GEE) models. GEE methods were applied to estimate model parameters using a binomial distribution for the variance function, a logit link function, and accounting for clustering via an assumed exchangeable working correlation structure (65). The outcomes will be used as dependent variables (one for each model) and, as independent variables, the intervention arms (no-framed, gain-framed, loss-framed message), the factors time (T0, T1, T2), the covariates (risk perception categories) and their corresponding interaction term. The other potential confounders (i.e., variables with baseline imbalances, study sites) will be added as independent variables to adjust GEE model. An exchangeable working correlation structure will be assumed in order to assess the association between factors and outcomes. The statistical significance of each parameter in the model will be analyzed using a Wald test. To account for the potential occurrence of type 1 errors, a Bonferroni correction will be implemented for all GEE models, with a *p*-value threshold of less than 0.003 indicating statistically significant differences (66). The final model’s results will be presented as estimated odds ratio (*OR*) and 95% confidence interval (*CI*) for each significant prognostic variable. We will also conduct the sensitivity analysis to assess the non-response mechanism (67) and an attrition analysis (68) to identify the differential dropout rates and dropout by group interaction on sociodemographic and pretest variables that may pose a threat the equity of the findings (69). Subgroup analysis was performed for cases that did not pass the manipulation check. The principle of “intention to treat (ITT)” will be applied in conducting all primary and secondary outcome analyses. Moreover, the patterns of missingness would be recorded across variables and time points to provide insight into non-random missingness. Statistical significance will be determined by results with *p* < 0.05 in two-sided tests. The analysis will be carried out using SPSS software for MAC (version 26.0) and R software (version 4.3.1).

The interview transcripts will be recorded, double transcribed, checked, and entered into NVIVO version 11 for analysis. Content analysis framework approach will be employed to analyze the qualitative data. To minimize potential bias, two experienced researchers will independently code the data. The identified concepts will be grouped into categories and themes.

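### Section 3.8.1 gives only a binomial-logit GEE over three visits, which does not suit 10-year CVD risk or most secondary outcomes

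*Protocol article*

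**What the plan says.** Section 3.8.1 (Data analysis) states that the differential changes in primary and secondary "outcomes at T1 and T2, relative to T0, across the three groups will be assessed using generalized estimating equations (GEE) models". It glosses primary as healthy behaviours and secondary as risk perception. The estimation is specified as "using a binomial distribution for the variance function, a logit link function", with an exchangeable working correlation. "The outcomes will be used as dependent variables (one for each model"), and the independent variables are arm, "the factors time (T0, T1, T2"), risk perception category and their interaction. "The final model’s results will be presented as estimated odds ratio" with a 95% confidence interval. No other family, link or effect measure is given for follow-up data.

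The only other method named for continuous data comes directly after the baseline chi-square sentence: "The difference in continuous variables will be analyzed using either one-way analysis of variance (ANOVA) or a non-parametric rank-sum test".

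The outcomes are defined elsewhere:
- The Abstract calls the second primary outcome a risk value. For 10-year risk, section 3.7.1 adds: "Participants will be classified into three groups based on the China-PAR cut-off value" (below 5%, 5–9.9%, 10% or more). Lifetime risk has two classes, split at 32.8%.
- In section 3.7.2, risk perception, efficacy belief and knowledge come from a 26-item questionnaire. "The emotional response will be assessed using two items on a 10-point scale", with a total of 2 to 20. Blood pressure, glucose, waist and BMI are also listed, as is MACE at 3 months.
- Table 1 (section 3.7.3) marks 10-year and lifetime risk at T0 and T2, emotional response at T1 only, and MACE at T2 only.

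**The concern.** A binomial variance with a logit link describes a mean between 0 and 1. A BMI, a blood pressure or a raw questionnaire total lies outside that range. Risk perception is the section's own example of a secondary outcome under this model, yet the article states no binary cut for it. A three-class risk level is not binomial either. Entry at 5% or more (section 3.4.1) should also leave the lowest 10-year class empty at baseline.

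The time factor adds a second mismatch: the model asks for change at T1 and T2 from T0, and several outcomes are not measured at all three visits.

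What is at stake is prespecification. An analyst following section 3.8.1 would have to choose a model, a cut-off or a rescaling, and an effect measure for part of a primary outcome and most secondary outcomes, possibly after seeing data. The section goes down to family, link, working correlation and test, so an analysis plan that follows it would inherit the mismatch.

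**Working it through.** The plan gives no figure on this point to reproduce. The check sets each outcome's scale and visits against the stated model.

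**1. Scale and visits** (sections 3.7.1, 3.7.2 and Table 1)

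| Outcome | Scale | Visits | Binomial-logit GEE over T0/T1/T2 |
|---|---|---|---|
| Activity, diet, medication | yes/no | T0, T1, T2 | suits |
| Lifetime risk, two classes | yes/no | T0, T2 | suits, without T1 |
| 10-year risk, value | percentage | T0, T2 | only as a 0–1 fraction, without T1 |
| 10-year risk, classes | three ordered levels | T0, T2 | not binomial |
| Risk perception, efficacy, knowledge | scores | T0, T1, T2 | not unless rescaled or cut |
| Blood pressure, glucose, waist, BMI | continuous | follow-up records | does not suit |
| Emotional response | score 2–20 | T1 | wrong scale; no change from T0 |
| MACE | yes/no | T2 | no change from T0 |

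Counting items separately, the affected secondary outcomes are risk perception, efficacy, knowledge, blood pressure, glucose, waist, BMI, emotional response and MACE: 9. Smoking, drinking and subjective health status bring the list to 12.

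**2. Estimable terms**

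An arm × time model with three arms and three visits has 1 + 2 + 2 + 4 = 9 parameters. The number that can be estimated equals the number of arm-by-visit cells observed:
- three visits: 3 × 3 = 9, so all 9;
- T0 and T2 (absolute risk): 3 × 2 = 6, so the T1 main effect and the two arm × T1 terms drop out (9 − 6 = 3). The T2-versus-T0 contrast remains;
- one visit (emotional response, MACE): 3 × 1 = 3, arm differences only.

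Matrix ranks computed for these designs were 9, 6 and 3.

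**3. Trial fits on assumed data**

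A binomial-logit exchangeable GEE with these arm × time terms was run on simulated data, with 240 people and 80 per arm:
- BMI-like outcome, three visits: no convergence and no estimates.
- Score of 2–20 at T1: no convergence and no estimates.
- 10-year risk as a 0–1 fraction at T0 and T2: fitted, with finite arm × T2 terms; T1 terms not estimable.
- MACE at T2 only: degenerate estimates.

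These runs show whether the model can be fitted. They do not predict the trial's results.

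**4. Expected MACE**

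The documents give no event rate. Assume 10-year risks r of 5% to 15% and an observation time m of 3 to 5 months:

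expected events = 240 × [1 − (1 − r)^(m/120)]
- r = 5%, m = 3: 240 × (1 − 0.95^0.025) = 0.31
- r = 15%, m = 5: 240 × (1 − 0.85^0.0417) = 1.62

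With 0 to 2 events over three arms, at least one arm has none, and its odds ratio against another arm is zero, infinite or undefined.

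**5. Cost if scores were cut**

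A median split of a normal variable has efficiency 2/π = 0.637, a loss of about 36%. The plan proposes no such split, so this only indicates what one way of forcing scores into the stated model would cost.

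**The case against.** Five points can be made for the plan.

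- *Scope.* The glosses on primary and secondary outcomes are introduced by i.e. Read literally, they confine the GEE to healthy behaviours and risk perception; the rest would be unstated detail that a condensed article may leave out. The scope is therefore not certain. But one model per outcome, and the Bonferroni rule for all GEE models, favour the wider reading. Even on the narrow one, risk perception sits under a logit with no binary definition.
- *Continuous variables have a method.* The ANOVA or rank-sum sentence does not repeat the word baseline. Its position ties it to the baseline comparison, however. It also has no time, perception category, interaction or site, so it cannot serve the objective in section 2 of matching framing to risk perception.
- *Absolute risk can be modelled.* This stands in part. Lifetime risk split at 32.8% suits a logit, and 10-year risk as a fraction can be fitted as a fractional logit. A reader might infer that a primary outcome has no workable model, or that cutting into yes/no is the only way to run it. The documents support neither.
- *Change in absolute risk exists.* This stands. A reader might infer from the missing T1 value that change from baseline is undefined, but T2 against T0 is available. Only emotional response and MACE lack a change from T0.
- *The sample size rests on the lifestyle outcome.* Its component behaviours are binary and logit is right for them. That limits the reach of the problem but leaves the other outcomes where they are.

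**Conclusion.** The point holds as a misfit between a stated rule and the outcomes it is applied to. Section 3.8.1 is right for the binary behaviours and usable for two-class lifetime risk at T0 and T2. It is wrong for the 10-year risk classes, for unscaled scores and for physical measures. For the 10-year risk value it can be run only as a fraction, with an odds ratio that describes no event and with T1 terms that cannot be estimated. Emotional response and MACE cannot enter a change-from-T0 model at all.

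The size is part of one primary outcome and about 9 of 12 listed secondary outcomes, on the wider reading of the model's scope. The figure of 0.3 to 1.6 expected MACE rests on assumed 10-year risks of 5 to 15% over 3 to 5 months. A reader might infer a 36% loss of information in this trial; that would follow only from a median split, which the plan does not propose.

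**What to change.** Replace the single specification in section 3.8.1 with one by outcome type and available visits:

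- **Binary behaviours:** keep the logistic GEE over T0, T1 and T2, with odds ratios.
- **10-year and lifetime risk values:** a continuous-outcome model for the T2 value, adjusted for the baseline value, arm, perception category, the arm × perception interaction and site. Report mean differences, or ratios if risk is logged; the log scale is one acceptable option. If two-class lifetime risk is also reported, restrict its logistic GEE to T0 and T2.
- **Risk perception, efficacy and knowledge scores, blood pressure, glucose, waist and BMI:** an identity-link GEE or linear mixed model, with mean differences.
- **Emotional response:** a comparison of arms at T1 only.
- **MACE:** counts by arm.

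State also that the ANOVA or rank-sum sentence refers to baseline, if that is what is meant. The cost is wording and a few lines of code, with no change to data collection, visits or sample size. The choices should be fixed before outcome data are examined by arm.

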**Methods:**

A multi-center 3 × 3 factorial, observer-blinded experimental design was conducted. The participants will be assigned into three message-framing arms randomly in a 1:1:1 ratio and will receive an 8-week intervention online. Participants are aged 20–80 years old and have a 10-year risk of absolute CVD risk of at least 5% (moderate risk or above). We plan to enroll 240 participants based on the sample calculation. The primary outcome is the CVD prevention behaviors and CVD absolute risk value. Data collection will occur at baseline, post-intervention, and 3-month follow-up.

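### The planned GEE estimates an unconstrained difference of changes from T0 and so forgoes precision that the T0 value offers; its covariates should also be fixed in advance

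*Protocol article*

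**What the plan says.** All of this stands in the protocol article, section 3.8.1 (Data analysis), unless another place is named.

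- **Effect measure.** Differential changes in the "outcomes at T1 and T2, relative to T0, across the three groups will be assessed using generalized estimating equations (GEE) models".
- **Model terms.** The intervention arms are independent variables, together with "the factors time (T0, T1, T2), the covariates (risk perception categories) and their corresponding interaction term". T0 is therefore a response occasion. The T0 value of the outcome is not named as a covariate.
- **Model form.** Binomial variance, "a logit link function, and accounting for clustering via an assumed exchangeable working correlation structure".
- **Covariates.** Baseline variables are compared between the arms ("The distributions of categorical baseline variables will be compared using" a chi-square test; ANOVA or a rank-sum test for continuous ones). Then: "The other potential confounders (i.e., variables with baseline imbalances, study sites) will be added as independent variables". The section does not define an imbalance.
- **Availability of T0.** The abstract states: "Data collection will occur at baseline, post-intervention, and 3-month follow-up". Table 1 shows physical activity, diet and medication at T0, T1 and T2, and 10-year and lifetime CVD risk at T0 and T2. Under section 3.5 the envelope is opened only after the baseline assessments are complete.

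**The concern.** With an arm main effect and an arm-by-time interaction, the model estimates a separate T0 mean for each arm. T0 is measured before allocation, so randomisation makes those means equal in expectation. Estimating them freely puts the full sampling noise of T0 into every treatment contrast. The baseline value is used, but inefficiently. At stake is avoidable width in the confidence intervals for the primary behaviour outcomes.

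The second matter is the imbalance rule. In a randomised trial a baseline difference between arms arises by chance. A variable that happens to differ need not predict the outcome, and a strong predictor that happens to balance is left out. The list of adjusters, and so the reported model, is not settled until the baseline data have been seen.

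**Working it through.** **The plan's own figure.** Section 3.4.2 gives 198 evaluable participants for W = 0.20, alpha 0.05 and power 80%. A one-degree-of-freedom chi-square has noncentrality 7.849, so N = 7.849 / 0.20² = 196.2, that is 197, or 198 as a multiple of three. The figure reproduces on that basis. It contains no term for the baseline value or for ρ, so it neither supports nor contradicts the present point.

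**What the planned contrast is.** On one simulated two-arm, two-visit data set, a binomial logit GEE with exchangeable correlation and arm, time and arm-by-time terms gave an interaction coefficient of 1.0888. The difference between arms in the change of the observed logits was also 1.0888. The planned effect is thus an unconstrained difference of changes.

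**Variance, linear approximation.** Take unit variance at both visits and correlation ρ. Per participant:

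- planned change contrast: 2(1−ρ)
- baseline-adjusted contrast: 1−ρ²
- ratio, adjusted to planned: (1−ρ²) / [2(1−ρ)] = (1+ρ)/2

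| ρ (assumed) | planned 2(1−ρ) | adjusted 1−ρ² | ratio | saving | 198 × ratio |
|---|---|---|---|---|---|
| 0.3 | 1.40 | 0.91 | 0.65 | 35% | 128.7 |
| 0.5 | 1.00 | 0.75 | 0.75 | 25% | 148.5 |
| 0.7 | 0.60 | 0.51 | 0.85 | 15% | 168.3 |
| 0.9 | 0.20 | 0.19 | 0.95 | 5% | 188.1 |

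The last column is the number of participants who, analysed with baseline adjustment, would carry the information that 198 carry under the planned contrast. An analysis that ignores T0 altogether has variance 1 on this scale, so below ρ = 0.5 the planned contrast is noisier than making no use of baseline.

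**Check on the logit scale.** A simulation (6,000 runs per setting) used 66 per arm, a T0 rate of 30%, and follow-up rates of 30% against 45%, the last being the 50% relative increase in section 3.4.2. It compared the change contrast with a baseline-standardised marginal log odds ratio. Both averaged about 0.65 to 0.66, so they estimate the same quantity. The variance of the change contrast was 1.62, 1.39 and 1.22 times the other at ρ = 0.3, 0.5 and 0.7. The reciprocals, 0.62, 0.72 and 0.82, lie close to the linear 0.65, 0.75 and 0.85. The check had two arms and one follow-up visit, and ρ = 0.9 was not simulated. A further simulation that gave the arms one shared T0 mean, with assumed parameters, also moved in favour of using T0: power 29% against 39% at the 0.05 level.

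**The imbalance rule.** Section 3.8.1 adds the variables as independent variables, which reads as main effects. A time-invariant main effect cancels from a within-person change exactly in the linear complete-data case, and nearly so on the logit scale. A simulation under no effect used two arms of 66, three visits, 11 independent baseline variables of which four were prognostic, and an assumed entry rule of p<0.05. Type I error for arm by T2 was 5.6% with selection and 5.8% without. Where a variable entered, the estimate moved by 0.015 to 0.027 standard errors on average, and the verdict at 0.05 changed in about 0.5% of those runs.

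**The case against.** The planned analysis is a legitimate one. Randomisation keeps the difference of changes free of baseline-imbalance bias on average, and the trial calls itself a pilot. That stands: the point concerns precision and prespecification, not validity.

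The size of the gain is unknown. High ρ is plausible for medication taken from prescription records and for China-PAR risk over a short follow-up, and the saving is then small. This also stands, and is why the range must extend to 0.9.

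The gain is not wholly free either. With a logit link, T0 as a covariate changes the odds ratio from marginal to conditional on baseline. The two remedies therefore target different effects, and the plan must say which it uses.

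Three stronger readings are tempting and unsupported:

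- A reader might apply 0.05 to each listed baseline variable and treat the chance that one enters as inflated error. The protocol states no cut-off and does not say that the descriptive tests decide entry. The chance of entry is not an error rate, and the simulation shows no inflation. Selection uses baseline data only, and section 3.3 blinds the statistician to allocation.
- A reader might infer that all covariates are picked from the data. Study site and risk-perception category are already named.
- A reader might infer that this shows the trial to be below its stated power. The stated 198 does not depend on the baseline analysis, and nothing here tests it.

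On the other side, odds ratios are non-collapsible. In one simulation with assumed parameters, adding a single prognostic covariate moved the mean log odds ratio at T2 from 0.62 to 0.71, while the verdict at 0.05 changed in under 1% of runs. That supports fixing the list for clarity about what is estimated, but not a claim about the error rate.

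**Conclusion.** The concern holds as one of efficiency. The model in section 3.8.1 leaves the T0 means free by arm, and its contrast has 2/(1+ρ) times the variance of a baseline-adjusted one. Using T0 would save about 35% of the variance at ρ = 0.3, 25% at 0.5, 15% at 0.7 and 5% at 0.9. These figures rest on a linear approximation, equal variances at the two visits and an assumed ρ; the logit-scale simulation supports them from 0.3 to 0.7. They also take the interaction in section 3.8.1 to include arm by time, which the stated aim of comparing changes across the groups requires.

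The imbalance rule is a secondary weakness. It leaves the reported model open until baseline data are seen, but its effect on the arm-by-time contrast and its error rate is small.

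**What to change.** **Preferred.** Keep T0, T1 and T2 as responses in the GEE, but constrain the arms to a common T0 mean: drop the arm main effect and the arm-by-risk-perception term at T0, and let arm act only at T1 and T2. Risk-perception category, time and their interaction stay. This keeps the marginal odds ratio. The gain comes through the working correlation, so the exchangeable structure already planned should be kept rather than independence.

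**Alternative.** Model T1 and T2 only, with the T0 outcome as a covariate, and state that the odds ratio is conditional on baseline.

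**Covariates.** Replace the reference to variables with baseline imbalances by a fixed list: study site and risk-perception category, plus the T0 outcome if it is used as a covariate. Report baseline characteristics descriptively, and show imbalance-adjusted results only as a sensitivity analysis.

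**Cost.** A small change of wording, with no new data. If T0 becomes a covariate, the interpretation of the odds ratio changes.
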